# Transmission of SARS-CoV-2 during indoor clubbing events: A clustered randomized, controlled, multicentre trial protocol

**DOI:** 10.3389/fpubh.2022.981213

**Published:** 2022-11-04

**Keywords:** SARS-CoV-2, respiratory virus, nightclub, respiratory virus transmission, vaccine

## Abstract

**Introduction:**

The SARS-CoV-2 pandemic led to the implementation of several non-pharmaceutical interventions (NPIs), from closings of bars and restaurants to curfews and lockdowns. Vaccination campaigns started hoping it could efficiently alleviate NPI. The primary objective of the “Indoor Transmission of COVID-19” (ITOC) study is to determine among a fully vaccinated population the relative risk of SARS-CoV-2 transmission during one indoor clubbing event. Secondary objectives are to assess the transmission of other respiratory viruses, risk exposure, and attitudes toward COVID-19 vaccination, health pass, and psychological impact of indoor club closing.

**Methods and analysis:**

Four thousand four hundred healthy volunteers aged 18–49 years and fully vaccinated will be included in Paris region. The intervention is an 8-hour indoor clubbing event with no masks, no social distance, maximum room capacity, and ventilation. A reservation group of up to 10 people will recruit participants, who will be randomized 1:1 to either the experimental group (2,200 volunteers in two venues with capacities of 1,000 people each) or the control group (2,200 volunteers asked not to go to the club). All participants will provide a salivary sample on the day of the experiment and 7 days later. They also will answer several questionnaires. Virological analyses include polymerase chain reaction (PCR) of salivary samples and air of the venue, investigating SARS-CoV-2 and 18 respiratory viruses.

**Ethics and dissemination:**

Ethical clearance was first obtained in France from the institutional review board (Comité de Protection des Personnes Ile de France VII - CPP), and the trial received clearance from the French National Agency for Medicines and Health Products (Agence National de Sécurité du Médicament - ANSM). The trial is supported and approved by The Agence Nationale Recherche sur le SIDA, les hépatites et maladies émergences (ANRS-MIE). Positive, negative, and inconclusive results will be published in peer-reviewed scientific journals.

**Trial registration number:**

IDR-CB 2021-A01473-38. Clinicaltrial.gov, identifier: NCT05311865.

## Key points

Study of the transmission of SARS-CoV-2 in vaccinated persons in real life conditions participating in a nightclub.

## Introduction

### Transmission of respiratory viruses, including COVID-19

The SARS-CoV-2 is transmitted through virus-containing droplets (> 5 to 10 μm) and aerosols ( ≤ 5 μm) exhaled from infected individuals during breathing, speaking, coughing, and sneezing (1). It can be transmitted by asymptomatic infected individuals and during the incubation period (2). Superspreading events have been identified mainly in closed spaces, without wearing a mask with no test condition to enter (3). Moreover, the indoor transmission increases with the number of infected participants' time of exposure and lack of ventilation. The risk of transmission varies widely depending on the setting and activity (singing, eating…etc.), and has been originally reported to ranging from 10.3% in a train (4) to 78% in a church for the pre-alpha variant (5, 6). Seasonal respiratory viruses, such as influenza, respiratory syncytial viruses (RSVs), metapneumovirus, rhinovirus, adenovirus, bocavirus, adenovirus, and coronaviruses (NL63, HKU1, OC43, and 229E) are a concern because they can cause a heavy burden especially in new-born, elderly, immunocompromised patients, or with comorbidities. As for SARS-CoV-2 (7–10), these viruses are transmitted *via* droplets and aerosols, depending on temperature and humidity, following a “U” shape curve (10). However, there is a lack of data regarding their spread in indoor settings (11).

### The vaccine against COVID-19 and its efficacy in transmission for pre-alpha and alpha variant

COVID-19 vaccines have been shown to be highly effective (>90%) in preventing SARS-CoV-2 infections in pre-alpha and alpha variants, according to the data collected in the USA, UK, Israel, and Qatar. Moreover, observational data have also demonstrated their efficacy to prevent the disease, especially in healthcare and household settings (40–50%) (12).

### The vaccine against COVID-19 and its efficacy on the delta variant and its transmission

The approved COVID-19 vaccines have lower effectiveness against mild forms of SARS-CoV-2 infections but remain effective to prevent hospitalizations (13–15). Contrasting results have been published regarding the transmission of SARS-CoV-2 among vaccinated. Evidence of the COVID-19 outbreak in a large, vaccinated population have been reported in Provincetown (USA) (16), which has also shown a superspreading event, while transmission in a healthcare setting occurred in Vietnam (17). However, another study in the USA showed few work-related secondary cases in vaccinated healthcare workers. A recent prospective cohort study in the UK found a modest protective effect on COVID-19 transmission (18): The secondary attack rate (SAR) in household contacts exposed to the delta variant was 25 and 38% in vaccinated and unvaccinated contacts, respectively. SAR among household contacts exposed to fully vaccinated index cases (25%; 95% CI 15–35) was similar to household contacts exposed to unvaccinated index cases (23%; 15–31).

### Transmission of COVID-19 in indoor clubbing

Indoor clubbing events may pose a significant risk of SARS-CoV-2 transmission: there is no physical distancing between individuals when operating at full capacity. A high density of persons and interactions between individuals include high-risk behavior such as singing, dancing, or physical contact (19). In addition, without proper air filtration or air renewal systems, infectious aerosols may accumulate and lead to a superspreading event. In an unvaccinated population, these places can be at high-risk place of SARS-CoV-2 transmission (20). Few studies have looked at the transmission of SARS-CoV-2 in festive events but none in vaccinated people (15, 21–23).

### Rationale, knowledge gap, and issues

More research is needed to measure the transmission of the delta variant during indoor live events: current evidence shows that vaccines are less effective in preventing transmissions, depending on the context. Moreover, we need to study transmission in a real-life setting where tests will no longer be needed to participate in an event, because of cost and practical issues.

### Hypothesis and objectives

#### Hypothesis

Our study hypothesis is that the participation in an indoor clubbing event is not associated with an increased risk of transmission of SARS-CoV-2 in fully vaccinated participants, while other respiratory viruses' transmission is increased.

#### Objective

The primary objective is to assess the absence of an increase in the risk of SARS-CoV-2 infection 7 days after an indoor club event in the group participating in the event, being fully vaccinated and without a face mask, compared to a non-participating group.

## Methods and analysis

### Study design

The present protocol is designed according to the CONSORT statement for randomized controlled trials (24) and the complete version has been registered under the number “021-A01473-38” with the French research authorities. Randomized, open-label, non-inferiority interventional cluster study with 4,200 participants divided 1:1 into two groups of volunteers recruited *via* social networks and *via* nightlife professional union networks.

Participants must have the same types of social interactions that they might have outside of the study. Thus, randomizing participants individually would result in splitting groups of participants who planned to spend the evening together. Participants who are “alone” at a party would not behave as they would under real-life conditions with friends. On the online booking module, participants will be able to mention the email of the people with whom they want to participate in the experimentation.

Participants will be allocated by reservation groups of up to 10 people through a central electronic service (WEEZEVENT, (25)).

Participants will be randomized into two arms:

- Experimental group: Indoor clubbing event- Control group: No participation in the indoor clubbing event

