### Location of the study and event

The 2,200 participants of the experimental group will be randomly assigned to one of the two indoor venues called “La Machine du Moulin Rouge” or “La Bellevilloise.” The reservation group of participants will be assigned to the same venue to respect the randomization by block.

“Machine du Moulin Rouge” is a venue with a surface area of 500 m^2^. It has two bars and two ventilation systems: one at the central bar whose ventilation capacity is 10,627 m^3^/h, and another on the main stage whose capacity is 11,000 m^3^/h (Figure 1). “Bellevilloise” is a venue with a surface area of 450 m^2^ and has only one bar. Its ventilation system operates at 7,500 m^3^/h thanks to two machines located at the dance floor and bar levels (Figure 2).

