### Statistical considerations

#### Sample size computation

In a non-inferiority design, the sample size depends on the probability of the observed event (here a SARS-CoV-2 infection), the power of the study, and a threshold of clinical significance.

To define this threshold, we consider that the exposure of a vaccinated population to the event has to lead to an equal or less number of secondary infections than in a non-exposed unvaccinated population. However, according to the risk/benefit balance and the random assignment, both our control and intervention arms need to be fully vaccinated. Consequently, we need to estimate the level of infection which could have been observed in the control group if it had not been vaccinated. Assuming a vaccine efficacy against infection of 80% would mean that the risk of infection is divided by 5, hence we consider that the incidence observed in the control group could have been multiplied by 5 if the control group was not vaccinated. Consequently, we set the non-inferiority threshold to five times the incidence observed in the control group.

As shown in Figure 3, the additional risk could be detected as a function of incidence and sample size, with 80% power and alpha risk of 5%. We corrected observed incidence rates in the population to account for 38% under-detection and 80% vaccine protective effect, as observed in France in 2020 (28).

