**Figure 3 F3:**
[figure not shown]
Minimal detectable relative risk depending on the number of subjects in the intervention group for different levels of incidence of SARS-CoV-2 infection detected in the general population. With 2,000 subjects in each arm (intervention and control), we have a power of 80% to detect a relative risk of 3–4.4 depending on the level of SARS-CoV-2 incidence.

For incidences in the general population of between 100 and 300 positive tests per week per 100,000 people, the detectable excess risk would be between 4.4 and 3 (respectively) for 2,000 participants in the intervention group and 2,000 participants in the control group (ratio 1:1; Figure 3). We simulated the impact of the clustering effect, considering an increased risk of infection within groups of participants who came together to the event. Considering that the secondary attack rate within those groups would be decreased by 80% by the vaccine protection, we could assume that the intra-cluster correlation would be negligible and that the design effect would be close to 1. With a planned attrition rate of 10% of participants for the primary outcome on D7, we plan to randomize a total of 2,200 participants in the “experimental” arm and 2,200 in the “control” arm.

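### Study design gives a total of 4,200 where the abstract and the sample-size derivation give 4,400; separately, 2,200 people are allocated to two venues of 1,000 places with no statement of how the figures fit

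*Protocol article*

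**What the plan says.** All the places below are current text of the protocol article.

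- **Study design:** a "non-inferiority interventional cluster study with 4,200 participants divided 1:1 into two groups of volunteers", so 2,100 per arm.
- **Abstract, Methods and analysis:** "Four thousand four hundred healthy volunteers", randomized 1:1, with the experimental group described as "2,200 volunteers in two venues with capacities of 1,000 people each" and a control group of the same size.
- **Location of the study and event:** "The 2,200 participants of the experimental group will be randomly assigned to one of the two indoor venues".
- **Sample size computation (text after Figure 3):** the detectable relative risks of 4.4 to 3 are given "for 2,000 participants in the intervention group and 2,000 participants in the control group". The allowance for loss is worded "With a planned attrition rate of 10% of participants for the primary outcome on D7". It leads to a target of 2,200 for each of the two arms.

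The article does not explain 4,200. It also does not say how 2,200 allocated people relate to 2,000 places.

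**The concern.** A published protocol is the reference against which recruitment is later judged, so it needs one target. Two are printed, and they have different consequences: 4,400 roughly preserves the 2,000 per arm behind the power statement after the planned loss, and 4,200 does not.

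The capacity question is separate. The experimental arm is 200 larger than the combined capacity of the rooms. The only allowance in the plan is for the day-7 outcome, so it does not by itself account for people who do not come or are not let in. This matters for a non-inferiority trial analysed by intention to treat: people in the experimental arm who were never exposed pull the contrast towards no difference, which is the direction of the study hypothesis.

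**Working it through.** **Inputs.** 2,000 per arm for power, 10% loss at day 7, and 2,200 randomized per arm (Sample size computation). Total 4,200 (Study design). Total 4,400 and two venues of 1,000 (abstract). Non-inferiority threshold of five times the control incidence (Sample size computation).

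**1. The plan's own figure.** 2,000 × 1.10 = 2,200 per arm, and 2 × 2,200 = 4,400. This reproduces the abstract and the sample-size text exactly. It does not give 4,200.

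**2. Size of the contradiction.** 4,400 − 4,200 = 200, and 200 / 4,400 = 4.5%.

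**3. Evaluable number under each total.**

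| Total | Per arm | After 10% loss | Against 2,000 | Loss at which 2,000 remain |
|---|---|---|---|---|
| 4,400 | 2,200 | 2,200 × 0.90 = 1,980 | −20 (−1.0%) | 1 − 2,000/2,200 = 9.1% |
| 4,200 | 2,100 | 2,100 × 0.90 = 1,890 | −110 (−5.5%) | 1 − 2,000/2,100 = 4.8% |

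The 20 missing from the first row arise because the 10% was added to 2,000. Dividing instead gives 2,000 / 0.90 = 2,222.2, or 2,223 per arm, about 1% more than 2,200.

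**4. Does the 1% matter?** Assume, as an approximation, that the log of the detectable relative risk scales with 1/√n. Then at 1,980 per arm:

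- exp(ln 4.4 × √(2,000/1,980)) ≈ 4.43
- exp(ln 3 × √(2,000/1,980)) ≈ 3.02

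Both remain below the threshold of 5. The 4.4 and 3 themselves could not be reproduced, because the formula, the sidedness and the exact incidence correction are not shown. Nothing is concluded from that.

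**5. Venues.** 2 × 1,000 = 2,000 places for 2,200 people: 200 over, and 200 / 2,200 = 9.1%.

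**6. Illustration of dilution.** Suppose all 2,200 come, no place is reused during the night, and the 200 not admitted carry the control-group risk. With a true relative risk of 5 in those exposed, the intention-to-treat relative risk is (2,000/2,200) × 5 + (200/2,200) × 1 = 4.55 + 0.09 ≈ 4.6.

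**The case against.** The strongest reply is that 4,200 is a stray figure. The abstract, the venue section and the derivation all agree on 2,200 in the experimental arm, so the 1,890 describes a design that the derivation already excludes. That is largely right. It makes the correction editorial, but the printed total is still wrong, and 1,890 shows that the two figures are not interchangeable.

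On attrition, 2,200 is a conventional inflation and the shortfall is 1%. This stands: it is not a sample-size error.

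On capacity, a limit of 1,000 may apply to people present at one time. The abstract describes an 8-hour event, and the venue section lets participants arrive at any time. Some will not come. The Trial status section reports 1,216 included, about 608 per arm at 1:1, and at that number capacity would not bind, although the article does not say that enrolment had closed. The Strengths and limitations section also names venue capacity and adherence as limits on power. A journal article may leave ticketing detail to the full protocol. These points soften the concern, but they do not reconcile the two printed figures.

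Three stronger readings are tempting and not supported:

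- **That 200 people cannot be exposed.** This needs full attendance and no turnover, neither of which the article states.
- **That at most 1,800 would be exposed and evaluable (2,000 × 0.90).** This is not an upper bound. With a strict cap of 2,000 and 220 lost from the arm, the count is 2,000 − 220 = 1,780 if all losses fall among those admitted, and 2,000 − 20 = 1,980 if the 200 not admitted are among the losses.
- **That the plan requires 2,000 exposed and evaluable per arm.** It does not. The control arm is not exposed at all, and under intention to treat the number that counts is those randomized with a day-7 result.

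**Conclusion.** The contradiction in the total is established from the text alone: 4,200 in Study design conflicts with 4,400 elsewhere, and the derivation supports 4,400. Taken at face value, 4,200 would leave 1,890 per arm after the planned loss, 5.5% below the number behind the power statement. The gap between 1,980 and 2,000 is a 1% rounding point with no effect on the design, and there is no need to recompute Figure 3.

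The mismatch between 2,200 allocated and 2,000 places is also real as printed, and the day-7 allowance does not resolve it. Its effect cannot be sized from the article, which states neither the kind of limit nor the expected attendance. The dilution from 5 to about 4.6 marks what full turnout without turnover would do, assuming control-group risk in those not admitted. It is not a forecast.

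**What to change.** - Change the total in Study design to 4,400.
- After the 10% allowance, state that about 1,980 per arm are expected to be evaluable.
- In the abstract or the venue section, add a sentence saying whether 1,000 per venue limits people present at once or total admissions, and what non-attendance is expected, kept separate from loss at day 7.
- Confirm that anyone in the experimental arm who does not attend or is not admitted stays in that arm under the intention-to-treat analysis already specified.

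The cost is a few words of protocol text. No new sample-size calculation is needed and the design does not change. Because the trial has begun, the correction should be on record before recruitment and results are judged against the target.

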### Study population

Eligibility criteria are designed to select a sample from people attending parties, all in real-life conditions. The study focuses on individuals aged from 18 to 49 years without comorbidities to further reduce the risk of potential complications and transmission to people at risk.

#### Inclusion criteria

Patients must fulfill the following criteria prior to trial enrollment:

- Aged between 18 and 49 years old included without comorbidity- At inclusion, completed and checked vaccination defined at that time as:

° Two doses of vaccine (Vaccines Pfizer BioNTech^Ⓡ^/AstraZeneca^Ⓡ^/Moderna^Ⓡ^) at 4 weeks intervals plus 7 days.° Or one dose of Vaccine Janssen plus 4 weeks° Or in a patient with positive serology for SARS-CoV-2 (SARS-CoV-2 specific Ig G anti S and Ig anti N, by the enzyme-linked immunosorbent assay (ELISA) test, no rapid test accepted) or a history of proven infection: one dose of any COVID-19 vaccine plus 7 days

- People who declared to have no risk factor for severe COVID-19 according to the French Health High Authority (*Haute Autorité de Santé - HAS* (26))- People who declared not to live in the same place as someone with these risk factors- People residing in Paris region- People affiliated with the National health insurance (*Sécurité sociale*)

#### Non-inclusion criteria

Patients with any of the following criteria are not eligible for trial enrollment:

- Presence of symptoms of COVID-19 in the 2 weeks preceding the event- Pregnant woman or woman who declares not having an effective contraception method- Self-identification of medical conditions or comorbidities identified as a risk factor for severe COVID-19- People living with a person with these risk factors- Confirmed diagnosis of SARS-CoV-2 within 2 weeks before the event- Participants under tutorship or curatorship- Participants unable to give free and informed consent.

### Randomization

The randomization list will be centralized and computer-generated using permuted blocks of varying lengths. Patients will be randomly allocated to study arms by means of the central 24–7 Internet randomization service provider (KapCode^®^). The framework will be secured by a login and a password.

### Participant timeline

A communication campaign to recruit participants will be deployed *via* the social networks of partner artists and nightclubs. Posters and flyers will be distributed in five places in the capital.

Before inclusion, the participants will be able to pre-register for the event *via* a dedicated website https://revienslanuit.org/.

Participants will be asked to complete an initial inclusion questionnaire on the website.

Three days before the event (from D-4 to D-2), participants will have to register for an inclusion visit where they will have to pick up their reverse transcriptase-polymerase chain reaction (RT-PCR) SARS-CoV-2 saliva kits.

Two kits containing one tube to collect saliva samples (for D0 + D7) with prepaid envelopes will be given to all participants at this visit. An email address will be given to participants to inform investigators in case of bad realization of the test to get a new sampling kit. It will be explained to perform the test properly in case of symptoms.

It is during the inclusion visit that participants will have to show their up-to-date vaccination certificates.

All vaccinated participants will be included and randomized.

The day before the event, only participants in the experimental group will receive an email with a ticket for the event. For the control group, individuals are asked to respect current health measures and not to go to discotheques on the experimentation day. To facilitate their adherence to the protocol, they will receive compensation in the form of a gift voucher, given at the end of the last questionnaire.

- On Day 0, people randomized in the experimental group will come to the venue with their ticket and their saliva sample to participate in the event. At the entrance, they will have to show their certificate of vaccination and their ticket to the staff members. Individuals randomized in the control group would not be able to attend the event but they will have to send their saliva samples by mail.- On Day 1, participants randomized to the experimental arm of the study will receive a questionnaire to follow-up within 24 h after the party and those in the control group will receive a questionnaire to assess whether they also attended a party on the same day.- From Day 3 to Day 10, all participants will be monitored regularly *via* a short questionnaire to collect information on their health status and the possible appearance of symptoms suggestive of COVID-19. Email and SMS reminders will be sent in case of non-response.- On Day 7 (±1 day), all the participants (experimental group and control group) will have to send their D7 saliva sampling kit *via* mail. Upon receipt of this tube, the participants in the control group will receive compensation in the form of a gift certificate. In case of a positive test, participants will be contacted individually by the investigators' physician for contact tracing in the context of the research.

